# A three-armed cognitive-motor exercise intervention to increase spatial orientation and life-space mobility in nursing home residents: study protocol of a randomized controlled trial in the PROfit project

**DOI:** 10.1186/s12877-020-01840-0

**Published:** 2020-10-31

**Keywords:** Nursing home, Multi-modal intervention, Spatial navigation, Cognitive functioning, Physical activity, Life-space

## Abstract

**Background:**

In nursing home residents, the combination of decreasing mobility and declining cognitive abilities, including spatial orientation, often leads to reduced physical activity (PA) and life-space (LS) mobility. As a consequence of sedentary behavior, there is a lack of social interaction and cognitive stimulation, resulting in low quality of life. It has not yet been examined whether cognitive-motor training including spatial cognitive tasks is suitable to improve spatial orientation and, as a consequence, to enlarge LS mobility, and increase well-being and general cognitive-motor functioning. Therefore, the overall goal of this multicentric randomized controlled trial (RCT) is to compare the effect of three different intervention approaches including functional exercise and orientation tasks on PA, LS and spatial orientation in nursing home residents.

**Methods:**

A three-arm single-blinded multicenter RCT with a wait-list control group will be conducted in a sample of 513 individuals (needed according to power analysis) in three different regions in Germany. In each nursing home, one of three different intervention approaches will be delivered to participating residents for 12 weeks, twice a week for 45 min each: The *PROfit basic* group will perform functional strength, balance, flexibility, and walking exercises always at the same location, whereas the *PROfit plus* group changes the location three times while performing similar/the same exercises as the PROfit basic group. The *PROfit orientation* group receives navigation tasks in addition to the relocation during the intervention. Physical and cognitive functioning as well as psychological measures will be assessed in all study groups at baseline. Participants will then be randomized into either the intervention group or the wait-list control group. After 12 weeks, and after 24 weeks the measures will be repeated.

**Discussion:**

This study evaluates whether the three different interventions are feasible to reduce the decline of or even improve PA, LS, and spatial orientation in nursing home residents. By adding different training locations in *PROfit plus*, the program is expected to be superior to *PROfit basic* in increasing physical and cognitive parameters*.* Moreover, we expect the *PROfit orientation* intervention to be most effective in terms of PA, LS, and spatial orientation due to two mechanisms: (1) increased physical and cognitive activity will enhance cognitive-motor capacity and (2) the spatial training will help to build up cognitive strategies to compensate for age-related loss of spatial orientation abilities and related limitations.

**Trial registration:**

The trial was prospectively registered at DRKS.de with registration number *DRKS00021423** on April 16, 2020* and was granted permission by the Technical University Berlin local ethics committee (No. GR_14_20191217).

## Background

Nursing home residents frequently suffer from multimorbidity [1]. Especially in this high-aged population, progressive decline in motor and cognitive abilities often results in decreased quality of life [2, 3]. A large proportion of nursing home residents are physically inactive [4, 5] and spend their time alone [6]. Such physical inactivity has multiple negative consequences on health and well-being [7, 8]. Cognitive decline is a risk factor for reduced activities of daily living (ADL) and instrumental activities of daily living (IADL) in older adults [9, 10], which further contribute to a decreased quality of life. For example, declining cognitive abilities lead to functional limitations in performing fundamental physical and cognitive activities such as climbing stairs and producing intelligible speech [11].

It has been shown that the combination of decreasing mobility and declining cognitive abilities leads to an accelerated reduction of physical activity (PA) and life space (LS) [12–15]. Sedentary behavior hampers social interaction which in turn reduces cognitive stimulation [8]. Given the interplay between PA and cognitive abilities [16, 17], sedentary behavior aggravates cognitive impairment, leading to a vicious cycle. Beside these general impairments of cognitive abilities, age-related cognitive decline specifically affects spatial-cognitive abilities such as spatial orientation and navigation [18]. Decrements in these specific cognitive subdomains are early biomarkers of cognitive decline [19–21], with an adverse impact on mobility and, as a consequence, reduced LS mobility and PA.

LS mobility is a measure that has been positively associated with PA as well as social participation in nursing home residents [22] and – per definition – it also incorporates the use of someone’s spatial environment [23]. It was also shown to be positively associated with better cognitive function [24] and a predictor of cognitive deterioration [25, 26]. Spatial abilities underlying orientation in and navigation through the environment include remembrance of target localisation in an environment, awareness of distance and directions as well as the mental transformation of the relation between objects to own body positions and spatial orientation [27]. Spatial abilities are determined by factors of the individual’s lifespan development in various environments [28, 29] and decreasing spatial cognitive abilities can lead to reduced PA and a decreased LS mobility due to spatial anxiety [30]. However, not all spatial abilities in the aging population are affected to the same degree. To distinguish between general spatial abilities and spatial abilities that decline with increasing age, it is necessary to differentiate between egocentric and allocentric reference frames [31]. Within an egocentric reference frame, the environment is represented with regards to the current position and orientation of the person (e.g. the third door on the right leads to the dining room). Allocentric reference frames, in contrast, are centered outside the person (e.g. the dining room is located in the middle of the east wing of the building) and the spatial information is thus coded independently of the position and orientation of the person. While egocentric orientation strategies remain relatively stable in older age, allocentric strategies decrease considerably with increasing age [3, 32–34]. It seems that this reduction does not depend on individual preferences in using spatial orientation strategies across the life span [35]. During the last years, however, it has been repeatedly shown that the aging brain and body remain plastic and that older adults’ capacity can be improved through systematic motor or cognitive training [36–38]. By adding physical training components, cognitive resources can be addressed more effectively and/or flexibly [39]. Moreover, different types of dual- or multi-task training, for example combining motor exercises with unspecific orientation tasks, might positively influence the cognitive performance of older adults [37, 40]. These studies are complemented by psychological theories, for example, the resource theory [41], predicting that well-trained older adults have more resources available to perform cognitive tasks on a higher level. There is also evidence that specific training interventions will initiate mental stimulation and that mental compensation (e.g. through specific cognitive training like the method of loci) can enhance neural plasticity [38, 42].

However, some studies show that dual-task training is not always more beneficial than e.g. multicomponent exercises to gain positive effects on cognitive-motor performance in older adults [43–45]. To become more effective in improving dual-task performance, intervention programs should include a combination of complex balance and coordination tasks [46]. To optimize benefits for both, cognitive and motor functions, training interventions need to be task-specific [40, 47]. It has been shown that exercise programs including cognitive-motor elements (for example, using dual-tasking with specific muscle strengthening elements [48] to improve ADL components [49]) are more successful than cognitive or motor training provided separately. In addition, a recent study by Bherer and colleagues [50] emphasized the synergistic effects of the combination of cognitive and motor training. To achieve cognitive improvements through motor training, adaptation to participants’ individual prerequisites is important [39]. Adaptable exercise modalities are required to align exercises to individual requirements, which would thus allow for a comparable training intensity for all participants [39]. Hence, frequency, intensity, and duration have to be controlled. A recent meta-analysis revealed that cognitive-motor training should be provided for at least twelve weeks with a minimum of 60 min per week to improve executive functions [46]. Moreover, a progression that allows individual adaptions should be provided [39, 46].

The aforementioned vicious cycle of decreasing mobility and general cognitive decline can be addressed by cognitive-motor training. Previous studies that investigated training of motor function [51, 52] or spatial orientation [53, 54] demonstrated improvements in the physical and cognitive domain. Such interventions could enhance PA and LS mobility [55, 56], which may also stimulate overall cognitive performance. Moreover, Cassilhas and colleagues found that physical exercise (aerobic and resistance) improved spatial learning and memory [57]. However, it remains unclear whether these programs might induce stronger effects on cognitive-motor performance if specific cognitive components had been integrated [40]. In addition, animal studies on neurogenesis provided evidence that PA in combination with activity in cognitively enriched environments induces additive neurogenic effects in the hippocampus, an important underlying neural structure of human memory [58] and allocentric spatial orientation [59, 60]. Garthe and colleagues (2016) concluded that these findings underpin the physiological link between locomotion and orientation. Therefore, interacting with an enriched environment benefits cognitive functioning, including learning and memory abilities [61]. Moving through an enriched environment might specifically foster spatial learning as a means to enable individuals to re-orientate when confronted with the same environment [62, 63]. Moreover, in the context of long-term care Vance and colleagues [64] addressed different methods of cognitive training interventions (e.g. method of loci) to improve cognitive abilities such as orientation abilities or compensation strategies for the loss or limitation of cognitive strategies [64]. However, these methods have not yet become a standardized part of cognitive-motor interventions. One of the specific exercise components which have not been addressed in particular in nursing home residents is spatial orientation. It can be addressed via two different strategies within a training program. Firstly, physical training intervention can include dual-task elements addressing egocentric and allocentric aspects of spatial orientation. Secondly, integrating supportive spatial information like landmarks into care facilities is another means to compensate for decreasing spatial cognitive functions and to support the spatial orientation of nursing home residents [65]. In addition to landmarks that are given because of their functionality within the facility (e.g. social rooms, restaurant, etc.) or that are part of the immediate environment of the facility (trees, fountains, next bus stop, etc.), these supportive landmarks can be used within a training intervention to foster spatial learning based on distinct spatial reference frames.

It has not yet been examined whether cognitive-motor training including spatial orientation tasks is suitable to increase PA, enlarge LS mobility and to improve spatial orientation and, as a consequence, elicit changes in well-being and general cognitive-motor functioning in nursing home residents. Against this background, the overall goal of this multicentric RCT (PROfit) is to investigate the efficacy of three different intervention approaches on PA, LS mobility, and spatial orientation: The *PROfit basic* group will perform functional strength, balance, flexibility, and walking exercises at the same location, while the *PROfit plus* group relocates three times during the training. The *PROfit orientation* group receives navigation tasks in addition to the relocation during interventions. We hypothesize that all three intervention arms will generate slower decline or even improvements in residents’ PA, LS mobility, and spatial orientation compared to a wait-list control group. We assume that *PROfit plus* will be more effective than *PROfit basic* because of residents’ improved orientation due to the different training locations. Furthermore, we expect the *PROfit orientation* intervention to be most beneficial due to its additional focus on spatial orientation.

## Methods/study design

This protocol paper was drafted according to the SPIRIT statement [66].

### Trial design

Based on the existing research and the physical training recommendations mentioned above, a multicenter intervention study will be conducted, aiming to determine the feasibility and efficacy of three different exercise intervention programs for residents of nursing homes. The type of intervention program will be randomly assigned to the participating nursing homes. The participants’ allocation to the intervention or wait-list control group will be randomized after baseline assessment in each nursing home. The assessment of primary and secondary outcomes will take place upon entry to the study (T1) by a blinded assessor and will be repeated at twelve (T2) and at 24 weeks (T3) (see Table 1).

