### Data collection, management, and analysis

#### Statistical analysis

Descriptive data will be reported as group mean values and standard deviations or medians and interquartile ranges depending on the type of outcome and their distribution. Analysis of baseline differences will be performed using a multivariate analysis of variance (MANOVA). Parametrical and normally distributed measures will be analyzed in separate 4 (group: PROfit basic, PROfit plus, PROfit orientation, wait-list control group) × 3 (test: baseline assessment, post-allocation, close-out-testing) analyses of variance (ANOVA) with repeated measures. If baseline differences are detected, baseline assessment values as well as age and sex discrepancies will be included as covariates in the statistical model. In the case of statistically significant interaction effects, Bonferroni-adjusted post-hoc tests (t-tests, Wilcoxon tests) will be performed to detect statistically significant differences in the groups between baseline- and post-allocation-testing. Kruskal-Wallis and Friedman tests instead of ANOVA will be used for non-parametrical variables and for data for which normal distribution could not be assumed. The effect size will be determined using Cohen’s *f* [95] which is indicative of the effectiveness of treatment and helps to assess whether a statistically significant difference is of practical concern. Cohen’s *f* values are classified as small (0 ≤ *f* ≤ 0.24), medium (0.25 ≤ *f* ≤ 0.39), or large (*f* ≥ 0.40). Additionally, PS_dep_ scores (probability of superiority for dependent samples) will be computed as an estimate of effect size in non-parametrical post-hoc tests [96]. The significance level will be set at *p* < 0.025.

Intention-to-treat analysis will be conducted. For this purpose, data of all participants will be processed in the groups into which they were randomly assigned, regardless of whether they received or adhered to the assigned intervention. The majority of participants are expected to take part in a minimum of 80% of the training sessions. An additional per-protocol analysis will be performed if a sufficient number of participants are lost to outcome assessment or insufficient participation in training sessions. Multiple Imputation will be used to handle missing data assuming that data are missing by chance.

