#### Sample size estimate / power calculations

The required sample size was calculated with G*Power (Version 3.1.9.2, Heinrich Heine University of Duesseldorf) [97]. The following input parameters were used to obtain small-sized test × group interaction effects: effect size (f = 0.15), type I error (α = 0.05), type II error (1-β = 0.95), number of groups (*n* = 4), number of measurements (*n* = 3), correlation between measurements (r = 0.60). Additionally, a dropout rate of 30% (i.e., 20% lost to follow-up; plus 10% deceased) was considered. Our analysis resulted in a total sample size of 513 participants (i.e., 171 per center with 42–43 participants allocated to each group).

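### Programme type is randomised to nursing homes, but the 4 × 3 ANOVA and the power calculation treat the programmes as independent groups of residents, so home-by-time variation raises the false-positive rate above 0.025 by an amount that depends on the number of homes and the ICC

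*Protocol article*

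**What the plan says.** Two allocations take place at two levels. Under Trial design, programme goes to homes: "The type of intervention program will be randomly assigned to the participating nursing homes". Residents are then allocated within the home: "The participants’ allocation to the intervention or wait-list control group will be randomized after baseline assessment in each nursing home". The Abstract confirms that a home has a single programme: "In each nursing home, one of three different intervention approaches will be delivered to participating residents for 12 weeks". Under Interventions, wait-list residents later receive the programme assigned to their home.

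The Statistical analysis section puts both allocations into one factor, "4 (group: PROfit basic, PROfit plus, PROfit orientation, wait-list control group) × 3" occasions, in a repeated-measures ANOVA, with Kruskal-Wallis and Friedman tests as the fallback. The only adjustment is conditional on baseline differences being found: "baseline assessment values as well as age and sex discrepancies will be included as covariates in the statistical model". Neither home nor region appears. The significance level is 0.025.

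The sample-size section uses f = 0.15, α = 0.05, power 0.95, four groups, three measurements and r = 0.60, with 30% dropout: "Our analysis resulted in a total sample size of 513 participants (i.e., 171 per center with 42–43 participants allocated to each group". No ICC, cluster size or number of homes is given.

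Comparing programmes is part of the trial's purpose. The Background expects plus to do better than basic, and expects the orientation "intervention to be most beneficial due to its additional focus on spatial orientation". The Abstract and Discussion repeat this ordering.

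**The concern.** Which programme a resident receives is fixed by where the resident lives. Basic versus plus versus orientation is therefore a cluster-randomised comparison with the home as its unit. An ANOVA on residents takes its error term from variation between residents and counts each resident as an independent draw of the programme. If homes differ in how their residents change over the study (staffing, season, local routines, an outbreak), that variation enters the numerator of the interaction test but is not properly represented in the denominator.

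This comes from the unit of randomisation and would remain if every resident trained alone. It is separate from clustering by training session.

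At stake are the comparisons that are new in this trial. A chance difference in course between a few homes could be read as superiority of a programme, and the stated 95% power does not describe what the trial can detect between programmes.

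**Working it through.** **1. The plan's own figure.** For the within-between interaction, λ = f²·N·m/(1 − r), df1 = (4 − 1)(3 − 1) = 6, df2 = (N − 4)·2. With f = 0.15, m = 3, r = 0.60, α = 0.05 and power 0.95 this gives N = 127, or 128 with equal groups. Then 128/0.75 = 170.7, rounded up to 171, and 171 × 3 centres = 513. The match is exact but implies 25% dropout; 128 × 1.30 gives 167 per centre and 501 in all. Either way, only individual-level inputs enter.

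**2. Assumptions.**
- Completers: 513 × 0.70 = 359, taken as 90 per group.
- Homes: 9, 18 or 27 (3, 6 or 9 per programme). Nine is the minimum if a centre is a region and each region runs all three programmes. The upper end is near one training group per home: 513 × 3/4 = 385 trained residents, and 385/15 ≈ 26.
- ICC: the share of the variance of change that lies between homes, 0.01 to 0.10.

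**3. False-positive rate of the planned test.** The 4 × 3 interaction F test was simulated at nominal 0.025, with no programme effect, r = 0.60 and random home-by-occasion effects:

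| Homes | ICC 0.01 | 0.02 | 0.05 | 0.10 |
|---|---|---|---|---|
| 9 | 6% | 10% | 29% | 53% |
| 18 | 4% | 5% | 14% | 27% |
| 27 | 4% | 4% | 8% | 17% |

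Independent runs agree to within one or two percentage points. With only a constant home effect the rate was 2.7%, which is nominal within simulation error. If allocation within homes were 1:1 (60 completers per programme, 180 wait-list), the 9-home row would be about 5 / 7 / 19 / 38%.

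**4. Why it happens.** In units of the SD of change, with J homes and n completers per programme, the variance of a difference between two programmes is 2·ICC/J + 2(1 − ICC)/n. A resident-level analysis uses 2/n. For J = 3, n = 90, ICC = 0.05:
- True variance: 0.0333 + 0.0211 = 0.0544, SE 0.233.
- Resident-level variance: 2/90 = 0.0222, SE 0.149.
- Variance ratio: 2.45, which equals 1 + (30 − 1) × 0.05. The standard error is understated by a factor of 1.57.

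**5. Detectable difference between two programmes** (95% power, two-sided 0.025, ICC 0.05), computed as (t.9875 + t.95) × SE:
- Residents treated as independent: 3.91 × 0.149 = 0.58 SD of change.
- Direct comparison, 9 homes, 6 df: 4.91 × 0.233 = 1.15 SD.
- Direct comparison, 18 homes, 15 df: SE = √(0.0167 + 0.0211) = 0.194; 4.24 × 0.194 = 0.82 SD.
- Difference of own-home trained-minus-wait-list contrasts at 3:1 (30 + 10 or 15 + 5 completers per home): variance (2/J)(0.95)(1/m1 + 1/m0) = 0.0844 in both cases, SE 0.291. This gives 4.91 × 0.291 = 1.43 SD (9 homes) and 4.24 × 0.291 = 1.23 SD (18 homes). Fitting region with 9 homes leaves 4 df: 5.63 × 0.291 = 1.64 SD.

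**6. Does using the home as the unit repair it?** Comparing programmes on home-mean change gave rates of about 2 to 3% across these settings.

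**The case against.** Several stronger readings are tempting, and the article does not support them.

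- A reader might infer that false positives are certain to be far above 0.025. That depends on two quantities the article does not give. With 27 homes and an ICC of 0.01 to 0.02, the rate is only about 4%. Rates computed as if all 513 residents were evaluable would be higher still, but the plan itself expects 30% dropout.
- A reader might infer that any difference between homes, such as building or case mix, biases the result. Constant differences cancel in the interaction; only home-by-time variation matters.
- A reader might infer that intervention versus wait-list is compromised too. That allocation is randomised inside each home, so the within-home contrast is protected from home effects. The pooled four-group test, however, does not use that pairing.
- A reader might infer that 513 is too few. The stated inputs need 128. At ICC 0.05 the 359 completers carry the information of about 359/2.45 = 147 (9 homes) or 359/1.70 = 211 (18 homes), both above 128. This ignores the loss of degrees of freedom, fails at ICC 0.10 with 9 homes (359/3.90 = 92), and cannot repair a wrong error term.

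Two further points limit the weight. The planned post-hoc tests read as baseline-to-post comparisons within groups, so the inflation acts mainly through the omnibus interaction that opens the way to them. The Background words the ordering of programmes as an expectation, less firmly than the hypothesis against wait-list; yet the Abstract makes comparing the three approaches the overall goal.

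It might also be said that an article leaves such detail to an analysis plan. Here the model, its factor levels, its covariates and its fallback tests are all stated, so this is a stated choice and not an omission.

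**Conclusion.** The mismatch stands: the home is the unit of randomisation for programme, and both the analysis and the power statement use the resident. Whenever homes differ in change over time, the interaction test exceeds its nominal 0.025. The excess runs from slight (about 4% with 27 homes and ICC 0.01 to 0.02) to severe (about 53% with 9 homes and ICC 0.10). These figures assume about 360 completers in four equal groups and r = 0.60. The number of homes and the ICC are assumptions, so only the range should be quoted. The 0.95 power does not apply to comparisons between programmes. Because those comparisons are central to the trial and the remedy is a change of model, this should be corrected before the data are analysed.

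**What to change.** **Statistical analysis.** Replace the 4 × 3 ANOVA by a linear mixed model with random home and home-by-test effects. Test programme differences with home-level degrees of freedom (for example Kenward-Roger) and name this as the one primary estimator. The difference between homes' own trained-minus-wait-list contrasts is a different, less precise estimator and should be a sensitivity analysis at most. The Kruskal-Wallis and Friedman fallback also ignores home and needs a counterpart that respects it, such as a comparison of home-level summaries.

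**Sample size.** State that the 0.95 power for four independent groups does not apply to programme-versus-programme comparisons. Give the detectable difference for the chosen estimator and the actual number of homes over a range of ICCs. The values in step 5 of the working (1.15 or 0.82 SD for the direct comparison, 1.43 or 1.23 SD for own-home contrasts) show the order of magnitude and why estimator and figure must match.

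**Cost.** A change of wording and model, with no extra residents. Intervals for programme comparisons become wider and the stated precision less favourable, with fewer degrees of freedom still if region is also fitted.
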